##### Intervention costs

Costs to deliver the intervention, not including the research/assessment components, are used in the cost-effectiveness analysis. They are tracked during trial implementation and include the cost of counsellor time, intervention materials (workbook, pedometer, stretch band, scale) and related infrastructure (i.e., office space, telephones, computers and call costs).

### Patient safety

A number of strategies are used to ensure patients' safety. Intervention participants who identify new health concerns or questions about the medical management of diabetes are recommended to visit their GP to seek advice. Any participant who indicates suicidal ideation on the PHQ-9 scale is contacted by the project manager and informed that their GP will be notified and a 24-hour telephone crisis service number is provided. Adverse outcomes are also systematically monitored, as described below.

#### Adverse outcomes monitoring system

Adverse outcomes are assessed at each follow-up telephone interview by asking participants if they have had any new health problems since the previous contact, with the following examples provided: any new diagnoses of medical conditions or illnesses, such as a heart attack or cancer, any periods of hospitalisation or surgery, any muscle injuries, bone or joint problems, or any new symptoms or worsening of pre-existing conditions. Responses are recorded verbatim and then coded independently by two of the study investigators, first as "serious" (i.e., requiring hospitalisation) versus not, and then as "directly attributable to the study" (i.e., exercise-related pain or muscle injury, digestive disturbances related to dietary changes) versus not, with input on disagreements discussed with a researcher independent of the trial.

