#### Physical activity

A target of 210 minutes per week (30 minutes every day) of moderate-intensity, planned activity is encouraged, consistent with the level of physical activity necessary to promote weight loss [49]. Given evidence suggesting that even higher levels of activity (i.e., 60 minutes/day) may be necessary for weight loss maintenance [52], those who can do more activity will be encouraged to work towards this during the maintenance phase. The telephone counsellor works with participants to first identify types of activities that they enjoy and can be easily incorporated into their lifestyle (e.g., walking), rather than providing a structured exercise program [11,53]. As most participants are relatively inactive at baseline, increases in physical activity are initially small and gradually increase towards the goal of 30 minutes per day of moderate-to-vigorous intensity activity [49].

Resistance exercise (2-3 sessions/week) is also encouraged, as strength training has benefits for glycaemic control [54] and is consistent with the physical activity guidelines for older adults [55]. Participants are provided with a resistance band, and detailed photographs and instructions are included in the workbook with guidelines on the number of sets and repetitions of each exercise, along with options for progression.

In addition to daily planned physical activity, participants are encouraged to take opportunities to be active in and around their homes and workplaces (e.g. gardening, housework, taking the stairs), and to reduce sitting time (i.e., to get up and move every 30 minutes and to aim for no more than 2 hours/day of screen time outside of work). This is consistent with evidence on the health benefits conferred by light-intensity activity [56-58], and with newer evidence on the cardio-metabolic consequences of too much sitting [59,60].

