### Primary and secondary outcomes

Primary outcomes are: change in weight (kg), accelerometer-measured moderate-to-vigorous physical activity and glycaemic control (HbA1c). Secondary outcomes are: change in self-reported dietary and energy intake, accelerometer-measured light intensity and sedentary time, objectively measured waist circumference, percent body fat, fasting plasma glucose and blood lipids (total cholesterol, HDL-cholesterol, LDL-cholesterol, triglycerides), liver function enzymes, blood pressure, along with self-reported SCE constructs, medication use and health-related quality of life. We will also evaluate the incremental cost-effectiveness of the telephone intervention and examine demographic and health-related moderators of intervention effects and mediators consistent with the underlying theoretical basis. Related measures are described below and summarised in Table 3.

**Table 3 T3:** Summary of Measures

**Anthropometric**	**#**Weight****
	#Waist circumference
	% body fat
	
Cardio-metabolic	**Glycoslyated haemoglobin**
	Fasting blood glucose
	Cholesterol (total, HDL, LDL)
	Triglycerides
	Liver function tests (ALT, AST, LDH, ALP, GGT)
	Blood pressure
	Diabetes medication
	
Behavioural	#**Objectively measured physical activity (PA) via accelerometer**
	Average mod-vig PA/day (mins)
	Average light intensity PA/day (mins)
	Average very light intensity PA/day (mins)
	Average sedentary time/day (mins)
	Breaks in sedentary time (n/day)
	Bouts of moderate-to-vigorous intensity activity (n/day)
	Self-reported physical activity
	Walking (days & min/wk)
	Walking for exercise (days & min/wk)
	Moderate-vigorous PA (days & min/wk)
	Resistance training (days & min/wk)
	Sitting items (transport, television, computer min/wk)
	Self-reported diet
	Dietary intake (total energy, total fat, saturated fat, fibre)
	Dietary behaviour
	Sleep (duration & quality)
	
Psychosocial-Environmental	Depression
	Self-efficacy
	Social support
	Perceptions of the neighbourhood environment
	
Cost-effectiveness	Health-related quality of life
	Health care utilization
	Cost to deliver intervention
	
Intervention Delivery (tracked for each call)	Call duration
	Call completion

All assessed at baseline, 6, 18 & 24 months; #assessed at 12 months; bold text denotes primary outcome

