### Data collection

Data are collected via objective measurements conducted in participants' homes, telephone interviews, and self-administered questionnaires at baseline, 6-, 18-, and 24-months by research staff and registered nurses blind to participants' study group. At 12 months, weight, waist circumference and accelerometer-derived physical activity are also assessed. Home visits are conducted by registered nurses and include objective measurement of: height (baseline only; Seca 214 height rod, Seca, Germany), weight, waist circumference, body composition, blood pressure and collection of blood samples for biochemical assay. In addition, details of diabetes medications (drug and dosage) and any use (yes/no) of antihypertensive and lipid-lowering medications are also collected during this visit. Telephone interviews collect self-report data on: demographics (gender, age, education, income, type and number of chronic conditions; baseline only), and validated measures of physical activity, diet, quality of life and health care use, as well as items to assess sleep, diabetes history and management, use of weight loss aids and adverse outcomes. Self-administered questionnaires are used to collect data related to the social-cognitive and environmental constructs which underpin the intervention and to assess depression. In addition to the self-reported physical activity collected via the telephone interviews, accelerometers are used to collect objectively-measured physical activity and sedentary time. Data related to intervention delivery are also tracked by telephone counsellors following each call. This includes data on call outcomes (call completion versus missed calls), call duration and call content (via a checklist of topics). Details of the measures are provided below and summarised in Table 3.

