#### Behavioural outcomes

##### Objectively-measured physical activity and sedentary time

A dual-axis accelerometer (Actigraph model GT1M; Actigraph, LLC, Fort Walton Beach, Florida), fitted firmly around the waist by elasticised band and positioned on the right mid axillary line, is used to objectively-derive physical activity and sedentary time. Participants are instructed to wear the accelerometer during all waking hours (removing for any water based activities) for a continuous period of seven days, and to record time worn in a wear-time log. The study nurse demonstrates how to wear the accelerometer and complete the wear-time log. Research staff then telephone the participant to negotiate a start date and reiterate the instructions; the accelerometer and wear-time log are then posted to participants. On the (expected) seventh day of wear, a follow-up telephone call is made by research staff to ensure adequate wear time and to prompt accelerometer return in a reply-paid envelope. The protocol for the follow-up assessment is identical with the exception that the registered nurse does not repeat the demonstration and instructions at the assessment.

Accelerometer data are collected in one minute epochs. A generic program (SAS 9.1), modified from the National Cancer Institute [75], is used to identify outliers and summarise daily variables. The wear time syntax of the program, based on a combination of the wear-time logs and the accelerometer data, is modified for each participant in order to maximise the accuracy of the wear time estimation. Invalid days of observation (days with < 10 hours wear or excessive counts ≥ 20,000 counts per minute: cpm) will be discarded. Daily sedentary (< 100 cpm), very light-intensity activity (100 to 759 cpm), light-intensity activity (760 to 1951 cpm), moderate-intensity activity (1952 to 5724 cpm), and vigorous-intensity activity (≥ 5 725 cpm) [76,77] time are calculated and standardised for wear time using the residuals method [78]. Patterns of physical activity and sedentary time accumulation (for example, breaks in sedentary time [79] and bouts of moderate-to-vigorous intensity activity) [80] are examined. Data are reported as averages for valid days. The data collection and analytic protocol comply with the best-practice guidelines for conducting accelerometer-based activity assessments in field-based research [81].

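### Adverse outcomes are asked about at 6, 18 and 24 months but not at 12, so 12 of the 18 intervention months rest on one question with recall of up to a year

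*Protocol article*

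**What the plan says.** The subsection Adverse outcomes monitoring system, under Patient safety, describes how harms are collected: "Adverse outcomes are assessed at each follow-up telephone interview by asking participants if they have had any new health problems since the previous contact". Answers are written down verbatim. Two investigators then code them independently for seriousness and for attribution to the study. The examples given of attributable events are "exercise-related pain or muscle injury, digestive disturbances related to dietary changes".

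The Data collection section lists adverse outcomes among the items of the telephone interview and gives the timing, with assessors unaware of allocation: "telephone interviews, and self-administered questionnaires at baseline, 6-, 18-, and 24-months by research staff and registered nurses blind". The same section says what happens at one year: "At 12 months, weight, waist circumference and accelerometer-derived physical activity are also assessed". The footnote to Table 3 agrees: "All assessed at baseline, 6, 18 & 24 months; #assessed at 12 months", and the hash sign marks only weight, waist circumference and accelerometry.

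The intervention runs for 18 months, and months 7 to 18 are its maintenance phase. The Physical activity section notes that about 60 minutes a day may be needed to keep weight off, against a general target of 30, and adds that "those who can do more activity will be encouraged to work towards this during the maintenance phase".

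**The concern.** Read together, these sections give three structured looks at harms after baseline, with a gap of a full year between the first and the second. That gap covers most of the treatment period, including the months when some intervention participants are urged towards twice the earlier activity target.

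Two losses follow. First, the pain, strains and digestive upsets that the protocol would attribute to the intervention are easily forgotten over a year, so they are likely to be under-recorded. Second, someone who leaves for good between months 6 and 18 contributes no coded harm data after month 6, even if still under follow-up at the 12-month assessment.

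No other described source fills the gap. Counsellors' call records cover completion, duration and topics, not events, and exist only in the intervention arm. The health care use items look back six months, so at month 18 they do not reach hospital stays in months 6 to 12.

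**Working it through.** The protocol gives no figure for recall, so there is none to reproduce. The check is arithmetic on the stated schedule.

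**Inputs**
- Follow-up interviews at 6, 18 and 24 months (Data collection).
- Intervention length of 18 months (Purpose).
- 300 participants and 30% attrition (Sample size).
- Assumptions, not in the document: events spread evenly over treatment; attrition spread evenly over 18 months.

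**Intervals between looks**
- Now: 6 − 0 = 6, 18 − 6 = 12 and 24 − 18 = 6 months. The longest is 12 months, and 12/18 = 67% of the intervention.
- With a 12-month look: 6, 6, 6 and 6 months. The longest is 6 months, and 6/18 = 33%.

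**Treatment time more than six months before its question**
- Now: months 6 to 12, or 6/18 = 33%.
- With a 12-month look: none.

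**Mean recall over months 0 to 18, events spread evenly** (mean recall within an interval is half its length)
- Now: (6/18) × 3 + (12/18) × 6 = 1 + 4 = 5 months.
- With a 12-month look: 3 months.

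**Participants affected by attrition**
- Total lost: 300 × 0.30 = 90. Per month: 90/18 = 5.
- Lost in months 6 to 18, with no harm data after month 6: 5 × 12 = 60.
- Lost in months 12 to 18, who could have been asked at month 12 about months 6 to 12: 5 × 6 = 30. The range is 0 (all losses before month 12) to 90 (all after it).
- Still present at month 12: 300 − 60 = 240, range 210 to 300.
- If the same 90 are instead lost evenly over 24 months: 90/24 = 3.75 per month, giving 45 lost in months 6 to 18 and 22.5 in months 12 to 18.

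**What the previous contact could mean.** The term is not defined in the article.
- The previous interview: everything in months 6 to 18 is asked about once, with recall of up to 12 months. This is the natural reading and the one used above.
- The 12-month assessment: recall is at most 6 months, but no question covers months 6 to 12.
- The last counsellor call: the window is about one month in the intervention arm and much longer in usual care, which has no calls. Ascertainment then differs by arm.

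None of the three gives both arms complete coverage with short recall. The first is the mildest.

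**The case against.** The sections agree with one another, so this is a design choice and not a contradiction. On the natural reading nothing goes unasked. Serious events are defined by hospitalisation, and the question prompts for heart attack, cancer and surgery, which people seldom forget within a year. New activity, strength training and energy restriction begin mainly in months 2 to 6, which the 6-month look covers; the higher activity level is only for those able to do more. Participants are screened by their GPs and again by study staff, GPs receive assessment summaries, and intervention participants with new concerns are sent to their GP. The attrition figures depend on an assumed pattern: spread over 24 months they fall by a quarter, and the planned 150 per group for 115 needed allows only 1 − 115/150 = 23% loss. Any schedule of discrete looks loses data after the last completed one. A further open health question is also one more occasion on which blinded staff may learn the allocation.

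Much of this stands, and it limits the point. The argument concerns mainly minor events and completeness; day-to-day protection of participants is not in doubt, and the number affected by attrition is uncertain. It does not remove the point. The schedule itself creates the year-long window, no reading of the undefined term closes it, and even hospital stays in months 6 to 12 depend on one open question asked at least six months later.

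**Conclusion.** The concern holds. Structured harm data for 12 of the 18 intervention months (67%) come from one question at month 18, and a third of the intervention lies more than six months before the question that covers it. These two figures follow from the stated schedule, taking the previous contact to be the previous interview. The mean recall of 5 months assumes evenly spread events. The figure of about 30 participants never asked about months 6 to 12 assumes 30% attrition spread evenly over 18 months, and the range of 0 to 90 shows how far it depends on that. The document gives no event rate, so the number of events missed cannot be estimated. This is an avoidable weakness in the harm data that is worth correcting because correction is cheap. It does not threaten the primary or secondary outcomes.

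**What to change.** At 12 months, put the existing adverse-outcome question to both arms during the accelerometer call: "On the (expected) seventh day of wear, a follow-up telephone call is made by research staff to ensure adequate wear time". That call is already part of follow-up accelerometry, since "The protocol for the follow-up assessment is identical with the exception that the registered nurse does not repeat the demonstration". Record the answers verbatim and code them by the same two-investigator procedure.

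Replace the undefined reference to the previous contact with the last study assessment at which the question was asked: month 6 for the 12-month call and month 12 for the 18-month interview. This gives contiguous six-month windows. If the 12-month call is missed, the 18-month question reaches back to month 6, as it does now.

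No new visit, staff or committee is needed. At an assumed 5 minutes per call (range 2 to 10), the time is 240 × 5/60 = 20 staff hours over the whole trial. The low end is 210 × 2/60 = 7 hours and the high end 300 × 10/60 = 50 hours. Coding the extra answers comes on top.

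There are two other costs. Each call adds one occasion on which an answer could reveal the study group, a risk of the same kind as in the existing interviews. Participants already past month 12 when the change is made keep three looks, in both arms alike.

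### 'Serious' adverse outcomes are defined by hospitalisation alone, and the self-report system as described cannot capture deaths

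*Protocol article*

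**What the plan says.** The section 'Adverse outcomes monitoring system' describes three steps.

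- **Ascertainment.** "Adverse outcomes are assessed at each follow-up telephone interview by asking participants if they have had any new health problems since the previous contact". The prompts offered include new diagnoses, hospital stays, operations, musculoskeletal problems and worsening of existing conditions.
- **Coding.** "Responses are recorded verbatim and then coded independently by two of the study investigators". Seriousness comes first, under the rule "i.e., requiring hospitalisation) versus not". Attribution to the study comes second, under the rule "i.e., exercise-related pain or muscle injury, digestive disturbances related to dietary changes) versus not".
- **Disagreements.** These are handled "with input on disagreements discussed with a researcher independent of the trial".

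Three other sections bear on the point. 'Data collection' states that the staff and nurses who collect data are blind to study group. 'Usual care' states that the GPs of all study patients are sent summaries of assessment results. 'Incremental cost-effectiveness' builds a small probability of death into the Markov model.

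**The concern.** The programme encourages unsupervised physical activity and reduced energy intake in people aged up to 75 with type 2 diabetes, including insulin users. A reader of the trial report will want to know whether severe events were more common in one arm. That count depends on how 'serious' is defined and on which events can reach the coders.

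The definition uses place of care as a stand-in for severity. The two often agree but are not the same. Severe events treated at home, in general practice or without admission fall on the wrong side of the line, and planned procedures with an overnight stay also fall on the wrong side. The most severe outcome of all has no described way into the system, because the person who would report it cannot be interviewed. The reported count of serious events could therefore omit events that matter and include some that do not.

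**Working it through.** No arithmetic applies. The article gives no adverse-event rate, no death rate and no stated figure to reproduce. The check is to read the stated rule literally, apply it to types of event, and compare the result with the rest of the article.

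**Step 1: is hospitalisation the definition or an example?** The parenthesis begins with 'i.e.', not 'e.g.', and ends in a two-way split. Every reported event therefore goes to one side according to whether it required hospitalisation. No other section adds a criterion.

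**Step 2: apply the rule.**

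| Type of event | Reaches the coders? | Coded under the stated rule | Coded if severity were the test |
|---|---|---|---|
| Unplanned admission | Yes, if reported | Serious | Serious |
| Life-threatening event managed without admission | Yes, if reported | Not serious | Serious |
| Event causing lasting disability, no admission | Yes, if reported | Not serious | Serious |
| Elective admission | Yes; hospital stays and surgery are prompted for | Serious | Not serious |
| Death | Not through the described route | Not coded | Serious |

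The rule and a severity test agree in the first row only.

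**Step 3: can elective admissions occur?** Yes. 'Patient sampling and recruitment' screens out people planning a knee or hip replacement in the next 12 months, but follow-up runs to 24 months. That leaves 24 − 12 = 12 months in which even this one type of planned surgery is not screened for. Other planned procedures are not screened out in the same way, apart from bariatric surgery.

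**Step 4: can deaths be captured?** The described source is an interview with the participant about "any new health problems since the previous contact". The separate health care utilisation items also ask about hospital stays, but they too rest on the participant's answers. The economic section nevertheless expects that some participants may die. The article thus anticipates an outcome that its safety system, as described, does not collect.

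**Step 5: do the coding safeguards help?** Two coders working independently protect against slips and idiosyncratic judgement. They do not protect against the rule itself. Both will correctly code a non-admitted life-threatening event as not serious, they will agree, and the independent researcher will have no disagreement to discuss.

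**The case against.** The strongest reply has four parts.

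**This is a condensed article.** A full protocol may hold a wider definition and a procedure for deaths. For deaths this has force: the gap is in the system as described, and another route may exist. It does not answer the definition, which is stated here and is too narrow as stated.

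**Nothing is lost, only labelled.** "Responses are recorded verbatim", so severe events that participants mention are on file and can be recoded. This is right, and it is why the repair is cheap. It does not help with deaths.

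**Adverse outcomes are neither primary nor secondary outcomes, and no between-arm safety test is stated.** This is also right, and it limits the weight of the point. A count of serious events will still be read as a safety result.

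**Stronger readings go too far.** A reader might infer four things that the article does not support.

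- *Out-of-hospital deaths are coded non-serious.* That would follow from the definition taken alone, but a death would normally never reach the coders. The accurate statement is that deaths are not captured.
- *Attribution will follow arm because the coders are unmasked.* The article does not say that they know the allocation; it is silent. Data collection is masked, the events are "coded independently by two of the study investigators", and an outside researcher is consulted on disagreements. Attribution is defined by effects of the intervention's own components, so masking is worth stating, but no bias is shown.
- *The recall window differs by arm because the intervention arm has up to 27 counselling calls.* This needs 'previous contact' to include counselling calls. The interviewers are blind to group, so the natural anchor is the previous interview. Both arms also have nurse visits and accelerometer calls around assessments. Setting about two weeks against about six months is therefore not a sound comparison.
- *Up to 30% of participants have no safety interview.* The 30% under 'Sample size' is a planning allowance for attrition, in a calculation based on change to 18 months. Someone lost by then may have been interviewed at 6 months.

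**Conclusion.** The point holds for the definition and for the capture of deaths. The stated seriousness rule rests on hospitalisation alone and misclassifies in both directions: severe events without admission are under-called and elective admissions are over-called. As described, ascertainment by participant self-report cannot record a death, although the article's own economic model allows for one.

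The size cannot be given, because no event or death rate appears in the article. The direction of any effect on the comparison between arms is also unknown. The conclusion assumes that the published rule is the one the coders apply, and that no other route for deaths exists beyond what the article describes. Coder masking and the wording of the recall question are matters to clarify, not demonstrated errors. The primary and secondary efficacy analyses are unaffected.

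**What to change.** 1. **Redefine serious.** Code as serious any event that is fatal, life-threatening, leads to unplanned hospitalisation or causes persistent disability. Apply this to the verbatim responses already recorded, using the same two coders and the same procedure for disagreements.
2. **Count deaths by arm.** Use whatever notification the trial receives, for example through the GPs already in contact with it, and report deaths next to the coded events.
3. **Clarify, at little cost.** State that the two coders work without the allocation code. Verbatim text may still hint at the arm, so this masking may be incomplete; the text should not be stripped of content that the attribution judgement needs. Anchor the interview question to the last assessment interview.

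The main cost is a small amount of recoding, a tally of deaths and one reworded question. Some verbatim answers may not say whether an admission was planned; these should be flagged and not guessed. The sample size and efficacy analyses need no change.

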### Randomisation

Following baseline data collection, allocation to study groups (telephone intervention or usual care) is conducted using the method of minimization to ensure equal group balance across factors likely to impact on primary study outcomes [45,46]. Minimisation factors based on baseline data collection include: gender, age (< 55 years; ≥ 55 years), BMI (< 40 kg/m^2^; ≥ 40 kg/m^2^), HbA1c (< 8%; ≥ 8%), physical activity level (meeting guidelines of at least 150 minutes/week and 5 or more sessions; not meeting guidelines) [47], and diabetes management (insulin or combination therapy; traditional oral hypoglycaemic medications; new glucose-lowering medications (e.g. Byetta, Januvia); lifestyle alone). Allocation is performed using the free Minim computer software [48] and conducted by a research assistant with minor involvement in participant recruitment. The timeframe from participant recruitment to group allocation ranges from approximately three to eight weeks to allow for extensive baseline data collection (see Data Collection section below), and not all minimisation factors are known at recruitment (e.g. HbA1c level, diabetes management). Therefore, the ability for the staff member to predict with certainty, the allocation of participants at recruitment, a criticism of the minimisation method [46], is near impossible.

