#### Diet

Participants are encouraged to reduce energy intake by 2,000 kJ per day through individualised advice to allow for specific food preferences and approaches [10,12,61]. That is, the intervention does not use meal replacements or structured meal plans. Specific macronutrient compositions are not prescribed (e.g. high protein/low carbohydrate or high carbohydrate/moderate protein) as evidence on long-term maintenance of weight loss has shown similar outcomes for both types of diet [62-64]. A low fat diet (< 30%) is encouraged as this has been associated with long-term weight loss maintenance [52], as are a saturated fat intake of < 7% of energy and fibre intake of 25 grams/day for women and 30 grams/day for men, consistent with dietary recommendations for people with type 2 diabetes to reduce risk factors for cardiovascular disease [65]. Strategies to reduce energy intake include - improving portion control (by reducing portion size or number of serves) and lowering energy density (by increasing intakes of low energy foods such as fruits and vegetables and reducing intake of energy dense foods such as high fat foods). Regular meal patterns with an emphasis on eating breakfast are promoted [66].

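### Read literally, the definition of study-attributable harm has no place for hypoglycaemia, and the adverse-outcome question does not name it, although users of glucose-lowering drugs are enrolled

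*Protocol article*

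**What the plan says.** The protocol article describes the capture and coding of harms in one section, Adverse outcomes monitoring system.

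- **Question.** "Adverse outcomes are assessed at each follow-up telephone interview by asking participants if they have had any new health problems since the previous contact". Prompts follow, and they are expressly illustrations ("with the following examples provided"). They cover new diagnoses, hospital stays, surgery and musculoskeletal injury, and end with "any new symptoms or worsening of pre-existing conditions". Answers are taken down verbatim.
- **Coding.** Two investigators code each answer independently. The first code is seriousness ("i.e., requiring hospitalisation) versus not"). The second is attribution to the study (again with *i.e.* and *versus not*, around the list "exercise-related pain or muscle injury, digestive disturbances related to dietary changes"). Disagreements are discussed with a researcher independent of the trial.

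Three other parts of the article bear on the point.

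- **Population.** The Randomisation section has a minimisation level for "insulin or combination therapy" and another for oral hypoglycaemic drugs. Insulin is not among the exclusions under Patient sampling and recruitment, and insulin use is named as a possible moderator.
- **Intervention.** The Diet section states: "Participants are encouraged to reduce energy intake by 2,000 kJ per day". The Physical activity section sets a target of 210 minutes of planned activity per week. The overall aim is an HbA1c below 7%.
- **Timing.** Under Data collection, telephone interviews take place at baseline, 6, 18 and 24 months. The 12-month assessment is listed as weight, waist and accelerometry only.

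**The concern.** The attribution list recognises the musculoskeletal effects of exercise and the digestive effects of a changed diet. It does not recognise a glucose-related effect of either, although HbA1c is a primary outcome. The benefit of lower glucose is thus measured while the corresponding harm has no attributable category.

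The number of study-attributable harms is likely to be read as the safety result of an intervention that the authors hope to see translated into population health practice. If coders follow the definition literally, that number leaves out a foreseeable kind of event. If participants do not think to mention such events, the total number of reported harms is affected as well.

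**Working it through.** No calculation in the article bears on this point, so there is no stated figure to reproduce. The check traces a low-glucose episode through the rules as written.

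**1. Is the attribution list closed?** The two codes stand in the same sentence and are built alike: each is a label, an *i.e.* parenthesis and a *versus not*. The seriousness parenthesis is plainly a definition. By parallel, the attribution parenthesis is one too. Elsewhere the article uses *e.g.* when it gives examples, as with the weight-loss drugs, the newer glucose-lowering drugs and the moderators.

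**2. What happens to an episode?** Three cases:

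| Episode | Recorded? | Serious? | Attributable under the literal list? |
|---|---|---|---|
| Participant regards it as part of existing diabetes and does not mention it | No | – | – |
| Mentioned, no hospital stay | Yes, verbatim | No | No |
| Led to a hospital stay | Yes, through a direct prompt | Yes | No |

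The last column is the firm finding: under the literal rule no low-glucose episode is ever coded attributable, whatever its relation to the diet or activity changes. The first row is the softer finding: the wording makes omission likely but does not impose it.

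**3. How long is the recall?** Taking the previous contact to mean the previous interview, the windows are:

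- baseline to 6 months: 6 months
- 6 to 18 months: 18 − 6 = 12 months
- 18 to 24 months: 24 − 18 = 6 months

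The 12-month window spans the whole maintenance phase. Long recall affects every kind of harm, but an unprompted, non-hospitalised episode is among those most easily forgotten.

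**4. Does another part of the article fill the gap?** Not as described. Under Patient safety, intervention participants with new concerns are referred to their GP, which is not event recording. The call-tracking data listed under Data collection are call outcome, duration and topics covered. The interview also has items on diabetes history and management, but their content is not given. Hypoglycaemia as an event is mentioned nowhere; the nearest word is the name of a drug class in the Randomisation section.

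**The case against.** The best defence has four parts.

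- **The question is open.** Its prompts are only examples, and the last one, on new symptoms or worsening of existing conditions, fits a change in established diabetes. This stands. A reader might infer that the question shuts hypoglycaemia out; the text does not support that. It only fails to ask for it.
- **The closed list rests on an abbreviation.** The article is not strict in its use of *i.e.*: the Behavioural therapy section writes of some strategies in the plural and then names only self-monitoring. Two coders with recourse to an independent researcher might use judgement. This stands in part. If examples were meant, the wording is wrong and the correction is the same. If not, the rule misclassifies.
- **The arms can still be compared.** A reader might infer that no between-arm comparison of this harm is possible, or that an absence of reports would tell nothing. Neither follows. Nothing limits the question to one arm, verbatim answers can be counted by arm whatever their attribution code, and hospitalised episodes are prompted for and coded serious. Hospital stays are also collected under Health care utilisation. The comparison would be less sensitive, not impossible.
- **This is a condensed article.** A full interview script or coding guide may name the event. That is a fair answer to the missing prompt, though not to the attribution rule, which the article states in full.

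It is also tempting to quote an upper limit on risk from zero events among the 150 participants per group. The documents do not support one. It would ignore the 30% attrition assumed under Sample size, and it would include participants managed by lifestyle alone, to whom the argument does not apply.

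**Conclusion.** The point holds in a limited form. As worded, the attribution rule would code every reported low-glucose episode as not study-related, so intervention-related harm could be under-counted. The open question can capture such episodes, but under-reporting is likely because it does not name them and one recall window is 12 months.

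The size cannot be given: the article states neither the proportion on insulin or oral glucose-lowering drugs nor any event rate.

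The conclusion rests on three assumptions: that *i.e.* is meant literally, as the parallel definition of seriousness suggests; that the undescribed diabetes items do not ask about low-glucose episodes; and that such episodes are a plausible consequence of eating less and exercising more while on these drugs, which the article does not discuss. It concerns only how harms are elicited and counted. It shows no error in a primary outcome and no fault in clinical management.

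**What to change.** 1. Restate the attribution list as examples (*e.g.*) covering any harm plausibly related to the diet or activity changes, and include hypoglycaemia among them.
2. Recode the verbatim answers already held under the widened definition.
3. Add one prompted item on low-glucose episodes to the remaining follow-up interviews, with the same wording in both arms.
4. Report episodes by arm irrespective of attribution, with the attribution code as a secondary breakdown.

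The cost is about a minute per interview, one additional code and the recoding. There is also a methodological cost: recruitment began in February 2009, so a new item would mix unprompted and prompted reports across participants and visits. The two must be reported separately. Steps 1, 2 and 4 do not have this drawback and are worth doing even if the new item is judged too late. Nothing here changes the care of participants.
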